### Sample size calculation

2.5

The sample size for this trial is based on an expected mean difference between groups of 11 points of the Constant–Murley questionnaire, which is the minimum clinically important difference. To detect this difference between both treatments, with a value of *a* = 0.05 (probability of committing a type I error) and a statistical power of 95%, a minimum of 49 patients per group is needed. This minimal sample size estimate has been increased by 20% after considering the potential dropouts, finally including 60 patients for each group. Accordingly, the proposed experimental hypothesis is that there will be a difference of at least 11 points in the Constant–Murley questionnaire in the intervention group versus the control group. The sample size was determined using the Stata SE software, version 15.

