### Outcome measures

2.4

The assessment of scar area, color, hardness, thickness, itching, and pain was recorded for 8 weeks of treatment. Assess fatigue marks once a week and save case photos.

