#### Primary outcome measures

2.4.1

We will use the international scar evaluation method—“*Vancouver Scar Evaluation Scale*” as the main standard for evaluating the efficacy.

1.Color: 3 points for bright red, 2 points for light red, and disappear after pressing, 1 point for non-red or some gray, 0 points for normal skin color;2.Height of scar marks: 3 points above 9 mm, 5 mm < 2 points for height ≤9 mm, 1 point for 1 to 5 mm, 0 points for flat or slightly depressed;3.Hardness: 3 points for hard as cartilage, 2 points for hardness like rubber, 1 point for softness, normal for softness skin score: 0 points;4.Itching: 3 points for severe or persistent itching, 2 points for frequent and tolerable itching, sometimes 1 point for itching, and 0 points for no itching;5.Pain: very intense 3 points for the “hyperalgesia,” 2 points for moderate-intensity allergic pain, sometimes 1 point for pain, and 0 points for no pain;6.tightness: 3 points for strong tightness, not too tight strong and tolerable score 2 points, slight tightness score, no tightness score 0 points.

Efficacy index = (total score before treatment − total score after treatment)/total score before treatment × 100%.

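### Sample size, 95% power and hypothesis rest on 11 Constant–Murley points, which the trial does not measure, so power for the scar score is unknown

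*Protocol article*

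**What the plan says.** **Section 2.5 (Sample size calculation).** "The sample size for this trial is based on an expected mean difference between groups of 11 points of the Constant–Murley questionnaire". The 11 points are described as the minimum clinically important difference. With alpha 0.05 and "a statistical power of 95"%, the minimum is 49 patients per group. That minimum was "increased by 20% after considering the potential dropouts, finally including 60 patients for each group". The hypothesis is that "there will be a difference of at least 11 points in the Constant–Murley questionnaire in the intervention group versus the control group". No SD is given.

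**Section 2.4 (Outcome measures).** "The assessment of scar area, color, hardness, thickness, itching, and pain was recorded for 8 weeks of treatment".

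**Section 2.4.1 (Primary outcome measures).** The Vancouver scale is taken "as the main standard for evaluating the efficacy". Six items are listed, each with a top score of 3, and the section ends with "Efficacy index = (total score before treatment − total score after treatment)/total score before treatment × 100"%.

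**Section 2.3 (Interventions).** Participants are their own controls. Three scars are chosen in each patient: one untreated, one for group A and one for group B.

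**Section 2.6 (Randomization and blinding).** Participants, not scars, are allocated to 2 groups.

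**The concern.** A sample size has meaning only for the outcome, contrast and design it was computed for. Here the target difference, the unstated SD behind it and the hypothesis belong to an instrument that appears in no outcome section. No Constant–Murley data will exist, so the hypothesis can be neither supported nor rejected.

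A reader who relies on the 95% would also believe that the scar comparison has been shown to be well powered. The document does not show this.

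The design adds a second mismatch. Two independent groups of patients, as in Sections 2.5 and 2.6, and three scars within one patient, as in Section 2.3, have different error variances and so different power for the same 120 patients.

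**Working it through.** **Inputs from Section 2.5:** difference 11, alpha 0.05 (sidedness not stated; two-sided taken, one-sided also tried), power 95%, n = 49 per group, 60 after the increase. **From Section 2.4.1:** six items with a maximum of 3, so the total runs from 0 to 6 × 3 = 18. **Not in the document:** any SD, or any target difference for the scar score or the index.

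**1. Reproducing 49.** With n = 2(z₀.₉₇₅ + z₀.₉₅)²(SD/Δ)² and Δ = 11, SD = 15 gives 2 × 3.605² × (15/11)² = 48.3, rounded up to 49. Solved backwards with the noncentral t, 49 per group and 95% power correspond to d = 0.736, so SD = 11/0.736 ≈ 14.95. One-sided, d = 0.669 and SD ≈ 16.4. The figure is therefore coherent for its own inputs. The defect is the instrument, not the calculation.

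**2. Does it carry over to the scar score?**
- *Raw total, 0 to 18.* The largest SD arises with half the scores at 0 and half at 18, which gives about 9. An SD of 15 cannot occur. Eleven points would be 11/18 = 61% of the scale.
- *Percentage efficacy index.* A difference of 11 percentage points with an SD near 15 is possible. Section 2.5 does not say this was meant, and gives no inputs for the index.

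**3. What 49 per group gives on the raw total, if the groups are independent.** The SDs and the 1.5-point difference are assumptions, used only to show the range.

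| Assumed SD | Difference with 95% power (0.736 × SD) | Power for 1.5 points |
|---|---|---|
| 2 | 1.5 | 95.7% |
| 3 | 2.2 | 68.8% |
| 4 | 2.9 | 45.1% |

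**4. How far the design matters.** A 20% loss is assumed for illustration, with two-sided 0.05 and 95% power.
- *Parallel groups:* 60 × 0.8 = 48 evaluable per group. Detectable difference about 0.74 SD.
- *Within patient:* 120 × 0.8 = 96 evaluable patients. The paired t test needs a mean difference of about 0.372 times the SD of the differences, which is SD × √(2(1 − ρ)) for within-patient correlation ρ.

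| Assumed ρ | √(2(1 − ρ)) | Detectable difference |
|---|---|---|
| 0.3 | 1.183 | 0.44 SD |
| 0.5 | 1.000 | 0.37 SD |
| 0.7 | 0.775 | 0.29 SD |

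At an assumed SD of 3, that is about 2.2 points in parallel groups against 1.3, 1.1 or 0.9 points within patients.

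**The case against.** The best defence is that the numbers are internally sound. Forty-nine per group follows from 11 points and an SD of 15, and 49 per group still has a meaning in SD units (0.736) whatever the scale. A journal article may also leave the SD to a fuller document. The arithmetic part of this stands. The rest does not help, because Section 2.5 is not silent: it names an instrument, a clinically important difference and a hypothesis that contradict Section 2.4.1. A fuller document could correct that only by contradicting the article.

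Four stronger readings are tempting and not supported:

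- *The trial is underpowered.* The documents give no scar-score SD or target difference. Power could lie above or below 95%, as the tables show.
- *The implied SD is impossible for the primary outcome.* This is true of the raw total only. It does not cover the percentage index that Section 2.4.1 also defines.
- *The dropout step is wrong, because 20% loss from 60 leaves 48, below 49.* Section 2.5 describes an increase of 20%, not a 20% loss rate. 49 × 1.2 = 58.8, which 60 covers. Even if a 20% loss is supplied, power at the same d is 94.6%.
- *The corrected hypothesis must be group B versus group A on the week-8 total.* No primary contrast is named. Section 2.5 words the comparison as intervention versus control, and Section 2.4.1 ends on a percentage index. The choice is the sponsor's.

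**Conclusion.** The point holds. Section 2.5 sizes the trial and words its hypothesis on an outcome that is not collected, so the hypothesis is untestable as written and the 95% power is not a statement about the primary outcome.

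The mismatch itself is read directly from the text and needs no assumption. The size of the consequence does. Under assumed SDs of 2 to 4 and independent groups, power for an assumed 1.5 points runs from 95.7% down to 45.1%. If the comparison is within patients, the detectable difference falls from about 0.74 SD to between 0.29 and 0.44 SD, for assumed correlations of 0.7 to 0.3. Whether 120 patients are too few, enough or more than enough cannot be decided from the document.

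**What to change.** 1. Delete the Constant–Murley difference and hypothesis from Section 2.5.
2. Reconcile Sections 2.3, 2.5 and 2.6 on whether the comparison is within or between patients. No power figure can be settled before this.
3. State the hypothesis on the scar total or the efficacy index, for a contrast that the sponsor names.
4. Replace the 95% claim with what the planned 120 patients deliver under a stated SD, plus a stated within-patient correlation if the comparison is paired. Give the resulting difference in points or percentage points. The values in step 4 of the working show the form; they are illustrations, not proposed inputs.

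**Cost.** Section 2.9 says that recruitment has not started, so this is rewording, together with a design decision that is needed anyway. The restated power may be less favourable than 95% for a small difference.

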**Methods/design::**

In this study, we will use our own front-to-back clinical research method. We plan to include 120 young and middle-aged female patients who meet the diagnostic criteria for pathological scars. The untreated pathological scars of the enrolled patients will be used as blank controls. The intervention group will be given conventional western medicine treatment and combined Chinese and western medicine treatment. The assessment of scar area, color, hardness, thickness, itching, and pain was recorded for 8 weeks of treatment.

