### Interventions

2.3

The participants included in the observation will be self-controlled, and each patient randomly selected 3 different scar treatment areas at the same site as observation specimens.

Control group: Take the untreated pathological scars of the participants as blank control. This group will not give any intervention.

Intervention group: Among the two pathological scars, group A will be treated with conventional external medicine of western medicine, and group B will be treated with oral TCM decoction combined with conventional external medicine of western medicine. The main components of the TCM prescription are: *Baizhi, Jiazhu, Leiwan, Maidong, Yuanhu, Taoren, Honghua*, and *Jingjie*. Specific treatment method: clean the scar area, apply gel to the affected area, every 3 times. TCM decoction is taken orally after meals, 3 times a day. The total application time will be 8 weeks. At the same time, closely monitor the change of the condition in order to control the deterioration of the condition in time (Fig. 2).

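### The sample size counts two groups of 60 patients, but the interventions section has every patient supply all three conditions, so the stated group size and 95% power are not those of that comparison

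*Protocol article*

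**What the plan says.** Section 2.5 plans for an "expected mean difference between groups of 11 points of the Constant–Murley questionnaire". With alpha 0.05 and 95% power it states that "a minimum of 49 patients per group is needed". This is "increased by 20% after considering the potential dropouts", "finally including 60 patients for each group". The abstract's 120 patients equal 2 × 60. Section 2.6 has the same structure: a computer-generated sequence assigns participants to two groups, and each patient's group is kept in a sealed envelope.

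Section 2.3 describes a different unit: "The participants included in the observation will be self-controlled, and each patient randomly selected 3 different scar treatment areas". One scar is left untreated, one receives the conventional western external medicine (A), and one receives that medicine plus an oral Chinese-medicine decoction (B). The abstract agrees: "The untreated pathological scars of the enrolled patients will be used as blank controls". Section 2.2.2 fits this too, since it requires at least three scars per patient.

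**The concern.** A two-group calculation takes its precision from the between-patient SD and the number of patients in each group. In a self-controlled design every patient is in every condition, so precision comes from the SD of the difference between two scars of one patient. Section 2.5 states a per-group count and a power for the first structure, while section 2.3 describes the second. If section 2.3 is the design, a reader cannot tell what difference the trial can detect, and the enrolment target does not follow from the stated power. Replacing the questionnaire by the scar score would not cure this if the two-group formula were kept for a within-patient comparison.

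**Working it through.** **Inputs from section 2.5.** Difference 11 points, alpha 0.05, power 95%, n = 49 per group, increase of 20%, final 60 per group. **Assumed, because not stated:** a two-sided test, the SD, and the correlation ρ between two scars of one patient.

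**1. The plan's own figure.** With no SD given, 49 can only be back-solved.
- Normal approximation, n = 2(SD × (1.960 + 1.645)/11)². An SD of 15 gives 48.3, rounded up to 49.
- Two-sample t-test solved at n = 49: d = 0.736, so SD = 11/0.736 ≈ 15.
- Dropout: 49 × 1.2 = 58.8 and 49/0.8 = 61.25. The stated 60 is close to both, so there is no slip here.

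The figure of 49 is therefore consistent with a comparison of two independent groups with an SD of about 15. Section 2.5 does not name the formula. This is inferred from the per-group wording, the total of 2 × 60 and section 2.6.

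**2. If section 2.3 is the design.** The standardised within-patient difference is dz = d/√(2(1 − ρ)). Paired t-test, two-sided alpha 0.05, 95% power:

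| ρ (assumed) | dz | Patients in total | × 1.2 | ÷ 0.8 |
|---|---|---|---|---|
| −0.2 | 0.475 | 59.6 → 60 | 71.5 | 74.5 |
| 0 | 0.520 | 49.98 → 50 | 60.0 | 62.5 |
| 0.3 | 0.622 | 35.6 → 36 | 42.7 | 44.5 |
| 0.5 | 0.736 | 26.02 → 27 | 31.2 | 32.5 |

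The plan has 120 patients. A 20% loss leaves 120 × 0.8 = 96 complete patients. Power with 96 pairs is 99.9% at ρ = 0 and higher at any positive ρ. At ρ = −0.2 it is 99.6%.

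**3. If section 2.6 is the design.** Two-sample t-test with d = 0.736: 94.6% power at 48 per group (60 less 20%) and 97.9% at 60 per group. The two-group form then fits, and sections 2.3 and the abstract are what is wrong.

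**4. Limit on all these figures.** The value d = 0.736 comes from 11 points on the Constant–Murley questionnaire. The primary outcome in section 2.4.1 has six items scored 0 to 3, a maximum of 6 × 3 = 18. None of the powers above is the power for the scar score. They show only how far the two structures differ on the plan's own inputs.

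**The case against.** The strongest reply is section 2.6. If patients really are randomised to two groups, a two-group calculation is the right form and 60 per group roughly supports the stated power. This stands. A reader might infer that the stated size fails on every reading of the design, but the documents do not support that. The defect is that sections 2.3, 2.5 and 2.6 disagree. A version with three separate groups of 40 patients appears nowhere in the protocol, so its power is not evidence against the plan.

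A reader might also infer that 120 is at least twice what is needed. That is too strong. At ρ = 0 the need is exactly half of 120 with the × 1.2 convention, but 62.5 with ÷ 0.8. At ρ = −0.2 it is about 72. With alpha divided by three for three pairwise scar comparisons (an assumption) it is about 76 at ρ = 0 and 61 at ρ = 0.2, both with × 1.2.

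It can also be said that the wrong questionnaire is the more basic fault and will force a new calculation anyway. That is true, but a new calculation still needs the right unit.

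Finally, a simple switch to a paired B-versus-A contrast is tempting. The decoction in B is oral and may affect the same patient's other scars, so that difference may not isolate it. Section 2.5 also words its hypothesis as intervention versus control, so the contrast cannot be taken as settled.

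**Conclusion.** The point holds as an unreconciled design with a sample-size statement that belongs to only one side of it. Under the self-controlled design of the abstract and section 2.3, the stated 60 per group and 95% power are not those of the comparison made. On the plan's back-solved effect (two-sided alpha, an SD of about 15, non-negative correlation, one comparison at 0.05), about 50 patients or fewer before dropout would reach 95% power, and 96 complete patients would give about 99.9% or more. The error is therefore towards more patients, not an underpowered trial. The exact excess cannot be fixed from the document, because the SD, the correlation and an effect on the scar score are all absent. It should be corrected. Section 2.9 says that recruitment has not started.

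**What to change.** Reconcile sections 2.3, 2.5 and 2.6 on whether scars or patients are allocated, and name the contrast that is powered, taking into account that an oral treatment may reach all scars of one patient.

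- **If the self-controlled design stands:** replace the two-group calculation in 2.5 with a paired one on the scar score, using an assumed SD of the within-patient difference or a range of correlations. State the sample as 120 patients with three scars each, delete the 60-per-group statement, give the power or detectable difference for about 96 complete patients, and align 2.6.
- **If patients are randomised to two groups:** correct the abstract and 2.3, and restate the calculation in 2.5 on the scar score.

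The cost is one rewritten calculation paragraph, matching edits to the design text, and one rerun. No added patients are needed to correct the statement. The small downside is that an SD or a correlation must be assumed and stated openly.

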# A comparative study on the clinical effect of the treatment of pathological scars in young and middle-aged women with the combination of Chinese and western medicine

**DOI:** 10.1097/MD.0000000000020623

**Published:** 2020-06-19

**Keywords:** clinical trials, pathological scars, traditional Chinese medicine

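### Section 2.5 names two different contrasts, and the hypothesis it states (intervention versus untreated control) can be met when the Chinese decoction adds nothing

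*Protocol article*

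**What the plan says.** The title announces a study of the "treatment of pathological scars in young and middle-aged women with the combination of Chinese and western medicine". Section 2.3 (Interventions) sets out three scar conditions within each patient:

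- Untreated: "Control group: Take the untreated pathological scars of the participants as blank control".
- A: "Intervention group: Among the two pathological scars, group A will be treated with conventional external medicine of western medicine".
- B: "group B will be treated with oral TCM decoction combined with conventional external medicine of western medicine".

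A and B both stand under the label of intervention group. The abstract (Methods/design) does the same: "The intervention group will be given conventional western medicine treatment and combined Chinese and western medicine treatment".

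Section 2.5 (Sample size calculation) introduces its power statement with "To detect this difference between both treatments". Two sentences later it gives the hypothesis as a difference of at least 11 Constant–Murley points "in the intervention group versus the control group". No sentence states a hypothesis for B against A. Section 2.7 (Statistical analysis) mentions only a general between-group comparison by MANOVA. Section 2.6 randomises participants, not scars, to two groups.

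**The concern.** The external medicine is common to A and B, so only the difference between them can show what the decoction contributes. A hypothesis set against an untreated scar answers another question: whether some active treatment is better than none. The power sentence points to one contrast and the hypothesis sentence to another, and nothing elsewhere in the protocol says which is primary.

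The main conclusion is at stake. A result that meets the stated hypothesis is compatible with an inert decoction and an effective external medicine, so it could not carry a statement about the benefit of adding Chinese medicine.

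**Working it through.** **1. The plan's own figure.** Inputs from section 2.5: difference 11, alpha 0.05, power 95%, 49 per group, raised by 20% to 60. Neither an SD nor the sidedness is given. For two independent means, n = 2 × (z_alpha + z_power)² × SD² / difference². Solving for the SD with a two-sided test:

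SD = 11 × √(49/2) / (1.960 + 1.645) ≈ 15.1

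An SD from 14.95 to 15.10 gives 49 after rounding up (16.39 to 16.55 if one-sided). So 49 can be neither confirmed nor refuted. For dropout, 49 × 1.2 = 58.8, giving 59, and 49 / 0.8 = 61.25, giving 62; the stated 60 lies between.

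**2. What each reading estimates.** Let g be the effect of the external medicine and d the added effect of the decoction, both as improvement over an untreated scar, and suppose for now that the decoction acts only on the B scar. The values of g and d are assumed for illustration.

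| Contrast | Expression | g = 4, d = 0 | g = 0, d = 4 |
|---|---|---|---|
| A − untreated | g | 4 | 0 |
| B − untreated | g + d | 4 | 4 |
| A and B averaged − untreated | g + d/2 | 4 | 2 |
| B − A | d | 0 | 4 |

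The first three rows are the possible readings of intervention versus control. All contain g, and all are positive when d = 0. Only the last row isolates d.

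At the plan's own effect size, let A and B each beat the untreated scar by 11 points. The average is (11 + 11)/2 = 11, so the hypothesis is met, while B − A = 11 − 11 = 0. With SD 15.1 and independent groups, power for the stated hypothesis is 95.0% at 49 versus 49, or 98.6% if A and B are pooled as 98 versus 49. A test of B against A would reject only at its 5% error rate.

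**3. The oral route.** Section 2.3 places all three scars in one patient. If the decoction acts equally on every scar and treatment is concurrent (an assumption), the effects are: untreated d, A g + d, B g + d. Then B − A = 0 whatever d is, and each treated-minus-untreated difference is g. If A and B are instead in different patients, the treated scars show g and g + d, and B − A = d is recovered.

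**4. Power for B versus A.** Same assumptions (SD 15.1, two-sided 0.05, independent groups):

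| B − A (points) | Power at 49 per group | N per group for 95% power |
|---|---|---|
| 11 | 95% | 49 |
| 8 | 75% | 93 |
| 5.5 | 44% | 196 |
| 4 | 26% | 371 |
| 2 | 10% | 1482 |

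These figures show direction only. They are in Constant–Murley points, whereas the primary scale in section 2.4.1 has six items scored 0 to 3, with a maximum of 6 × 3 = 18.

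**The case against.** Four objections deserve an answer.

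- **Pooling is not in the protocol.** A reader might infer that A and B are averaged into one arm, so that half of any decoction effect is lost. No sentence says so; section 2.3 lists them separately, and a MANOVA does not imply averaging. This stands: g + d/2 is one reading of three. The conclusion does not depend on it, because all three contain g.
- **The power sentence may already mean A versus B.** Only A and B are active treatments, so a difference between two treatments fits that contrast. This also stands, and a reader who infers that B versus A was never intended goes too far. But the hypothesis sentence says something else, and the two must be made to agree.
- **The labels in section 2.5 may not be those of section 2.3.** Sections 2.5 and 2.6 speak of two groups of patients and use a questionnaire that is not an outcome of this trial. That mismatch is real. Still, section 2.3 and the abstract supply the protocol's only definitions of these groups, and under them the hypothesis does not isolate the decoction.
- **B versus A fails within a patient.** Correct for an oral decoction that acts systemically, as step 3 shows. Rewording the hypothesis alone is therefore not enough. This narrows the remedy but does not rescue the stated hypothesis, which on that reading carries no information about the decoction at all.

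The stated aims also never name western medicine alone as comparator. However, sections 1 and 3 justify combined treatment by the hope of better efficacy, and the abstract promises evidence on the effectiveness of Chinese medicine. A comparison with no treatment cannot separate that from the external medicine.

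**Conclusion.** The point holds in this form: section 2.5 names two contrasts, and the one stated as the hypothesis can succeed when the decoction adds nothing. It rests on the group definitions in section 2.3 and the abstract and on simple additive algebra; it needs no particular values of g and d. At the plan's own size, an 11-point advantage over the untreated scar is compatible with a decoction effect of 0.

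The documents do not support saying that the plan pools the arms, that it rules out A versus B, or that a misleading claim will in fact be published. The power figures rest on a back-solved SD and a scale foreign to this trial, so there is no single corrected sample size. Because the contrast decides what the trial may conclude, it should be settled before recruitment, which section 2.9 says has not started.

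**What to change.** In section 2.5, replace the hypothesis with wording such as: the primary comparison is B (combined treatment) versus A (western external medicine alone) on the change in total scar score, as defined in section 2.4.1, from baseline to week 8. A versus untreated and B versus untreated are secondary. Added benefit of the combination is concluded only if B versus A is met. Drop the undifferentiated intervention group from the hypothesis, and align the power sentence with it.

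Reconcile section 2.3 with sections 2.5 and 2.6, so that A and B are compared between patients, in line with the two-group randomisation of participants already described. Say also whose untreated scars serve B versus untreated: by the algebra above, an untreated scar in a patient taking the decoction may itself carry d.

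Re-derive the sample size for B versus A on the scar scale, stating the SD, the expected difference and the sidedness.

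Cost: no additional type of measurement, but more than an edit of one sentence, since the allocation text must be settled too. B versus A is likely to be a smaller difference than treated versus untreated, so the stated 95% power may turn out less favourable or the required number larger.
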